### Statistical analyses

2.5

To determine whether Take it Personal!+ leads to a decrease in SU, data on SU gathered from the daily diary measures will be analyzed visually and by using time series analysis. Both within-person processes and between-person differences will be studied. Missing data will be imputed using Kalman filtering equations [39] with the R package imputeTS [40]. At least a medium effect size is expected (cf [18]). The results will be reported following the Single-Case Reporting guideline in Behavioral Interventions (SCRIBE) to make the study transparent, to facilitate replication, and to structure the paper.

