### Study design

2.1

Data will be collected within a non-concurrent multiple baseline across individuals design [26]. We will examine the effectiveness of Take it Personal!+ in ten participants with MID-BIF and SUD receiving care from healthcare organizations for people with MID-BIF and behavioral problems in the Netherlands. Participants will be randomly allocated to one of the five baseline lengths varying from 7 to 11 days. The onset of the treatment will be randomized, which will maximize internal validity [27]. The design consist of four phases: baseline phase (7–11 days), intervention phase (11 weeks), post-treatment (1 month), and a follow-up phase (3 months after the intervention). The study is conducted between spring 2019 and summer 2020. It is registered in the Netherlands Trial Register (Trial NL4935, registered July 2nd, 2019), and approved by the Faculty Ethics Committee of the Radboud University (ECSW-2019-033).

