### Outcomes

2.4

The primary outcome of this study is frequency and quantity of SU. SU will be assessed with daily diary measures during the baseline phase (7–11 days), intervention phase (11 weeks), and post-treatment (1 month). The daily diary method will be applied using a mobile application for cellular phones (Ethica) [31]. Every morning or evening, participants will receive a push notification to complete a short questionnaire within a determined time frame (i.e., varying from 240 min to 780 min). The time of the push notification and the time frame will be decided in consultation with the participant. The questionnaire consists of fifteen questions and is based on previous studies [32,33]. One item will assess the frequency of SU, ‘Did you use *the primary substance* today?’ measured by (1) ‘yes’ and (2) ‘no’ responses. If the participant answers positively, he or she will be asked the second open-ended question, to assess the quantity of SU, ‘How many times?‘. To monitor the frequency of other daily SU, participants will be asked the question, ‘Did you use another substance today?‘, measured by personalized response categories (e.g., (1) ‘no’, (2) ‘yes, alcohol’, (3) ‘yes, XTC’, (4) ‘yes, cocaine’, (5) ‘yes, something else’).

A briefing by the researcher on the daily diary method will take place the day before the start of the baseline phase. In this briefing, attention will be paid to the daily diary procedure, the privacy statement, understanding and personalization of the items, and the time of the daily push notification will be determined. On the second day of the baseline phase, the researcher will visit the participants to check whether the participants have any questions or problems with using the application. If needed, the researcher will plan a second visit later that week [34]. Moreover, during the entire study the researcher will contact the participants if they did not fill in a number of questionnaires. Part of the questions will also be discussed during treatment sessions, where the therapist will evaluate the procedure during the intervention phase.

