Additional information on SU will be collected using standardized questionnaires. At baseline, post-treatment, and follow-up, we will use the Substance Use and Misuse in Intellectual Disability - Questionnaire (SumID-Q) [35] to assess the frequency, quantity and severity of SU by the Alcohol Use Disorder Identification Test (AUDIT) [36] and the Drug Use Disorder Identification Test (DUDIT) [37].

To monitor treatment fidelity, therapists will fill out an evaluation form after each session. The form will assess 1) adherence to the manual, 2) dosage, and 3) program differentiation [38].

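### Applied to a diary that stops for good, the unqualified Kalman imputation rule fills the remaining weeks with a projection that is analysed as if observed

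*Protocol article*

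**What the plan says.** The outcome is defined in section 2.4 (Outcomes) of the protocol article: "The primary outcome of this study is frequency and quantity of SU". Its schedule is "SU will be assessed with daily diary measures during the baseline phase (7–11 days), intervention phase (11 weeks), and post-treatment (1 month"). Section 2.5 (Statistical analyses) says that "data on SU gathered from the daily diary measures will be analyzed visually and by using time series analysis", and its whole provision for missing data is "Missing data will be imputed using Kalman filtering equations [39] with the R package imputeTS [40".

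That sentence does not separate scattered missed days from a permanent stop. It sets no maximum gap, does not name the state-space model, and is not accompanied by a sensitivity analysis. No other section limits it.

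Two other provisions bear on the point, both in section 2.4. One concerns retrieval: "during the entire study the researcher will contact the participants if they did not fill in a number of questionnaires". The other is a source of information outside the diary: "At baseline, post-treatment, and follow-up, we will use the Substance Use and Misuse in Intellectual Disability - Questionnaire (SumID-Q"), with the AUDIT and DUDIT. The article describes these questionnaires as additional information and does not link them to imputed diary days.

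**The concern.** Inside a series, a Kalman smoother uses the days before and after a gap, and a short gap is filled sensibly. After the last answered diary only past data remain, and the method becomes a forecast. Nothing in the stated rule stops that forecast from running through the rest of the intervention phase and the post-treatment month.

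The situation is foreseeable from the article itself. Section 3.1 says that diary answers go to the therapist and are discussed in sessions, so diary and treatment are coupled. It also says that, to the authors' knowledge, daily diaries have not been used for this long in this population before. Relapse prevention is one of the treatment components in section 2.3.

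The primary outcome is at stake in a small study: "We will examine the effectiveness of Take it Personal!+ in ten participants with MID-BIF and SUD". Each series is a tenth of the evidence, and section 3.1 relies on how comparable the effect is across replications. That section also takes comfort from every phase having more than five data points. A fully imputed post-treatment phase would appear to meet that standard without one observation in it.

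**Working it through.** The article gives no drop-out figure and no sample-size calculation, so there is no figure of the plan's own to reproduce. The check asks what the stated rule does when a diary stops for good.

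**Inputs from the article.** Intervention 11 weeks = 77 days. Post-treatment 1 month, taken as 30 days. Total after baseline 77 + 30 = 107 days.

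**Assumed inputs.** Share of days with use: baseline B = 0.70, on treatment T = 0.40, after the stop R = 0.70. Last answered diary on treatment day d = 42.

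**Step 1, days filled.** (77 - 42) + 30 = 65, and 65/107 = 61%. For d = 21 it is 86/107 = 80%. For d = 63 it is 44/107 = 41%.

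**Step 2, truth.** Intervention mean = (42 × 0.40 + 35 × 0.70)/77 = 41.3/77 = 0.536. Change from baseline = 0.536 - 0.70 = -0.164. Post-treatment change = 0.70 - 0.70 = 0.

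**Step 3, flat projection.** Both phases sit at 0.40, so the change is 0.40 - 0.70 = -0.30 in each.

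**Step 4, range.** The overstatement under a flat projection is (R - T) × (77 - d)/77 in the intervention phase and R - T in the post-treatment phase.

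| d | R | Intervention, points | Post-treatment, points |
|---|---|---|---|
| 21 | 0.70 | 21.8 | 30 |
| 42 | 0.70 | 13.6 | 30 |
| 63 | 0.70 | 5.5 | 30 |
| 42 | 0.55 | 6.8 | 15 |
| 42 | 0.40 | 0 | 0 |
| 42 | 0.30 | -4.5 | -10 |

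The direction therefore depends on R. If use goes on falling after the stop, the projection understates the reduction.

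**Step 5, is a flat projection what the method gives?** Yes/no series were simulated with 9 baseline, 77 treatment and 30 post-treatment days, 60 series per setting. The missing tail was filled from structural time-series models fitted in Python, not with imputeTS itself. Assumed use was 0.70 at baseline, 0.30 on treatment and 0.70 after the stop.

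- Local-level model, stop on day 42: the filled tail was a flat line (standard deviation 0.000). Median post-treatment use was 0.33 imputed against 0.70 true, and median intervention-phase use was 0.33 against 0.48.
- Local-linear-trend model: for a stop on day 21 the median imputed post-treatment level was -0.94, an impossible value, with 5th to 95th percentile -2.14 to 1.48. For a stop on day 42 the median was 0.13, with -0.63 to 2.33. Errors go both ways. The run gave optimiser convergence warnings, so these spreads are indicative only.
- Local-level model with relapse days recorded before the stop (100 series): the median imputed post-treatment level was 0.32, 0.43, 0.55 and 0.63 after 0, 3, 7 and 14 recorded relapse days. The forecast moves back towards 0.70 as the diary captures the relapse.

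**Step 6, does truncation repair it?** Ending the series at day 42 leaves an intervention mean of 0.40, again -30 points. It removes the invented post-treatment month but not the intervention-phase error. Setting days 43 to 77 to the baseline level gives 0.536, or -16 points, and setting the post-treatment days to it gives 0. This matches the truth here because the example assumes a return to baseline.

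**The case against.** The strongest reply is that this is one condensed sentence in an article. Gap limits and drop-out handling are commonly left to a full protocol or analysis plan, and the sentence can be read as covering only missed days in an ongoing series. That stands to this extent: the article does not announce that whole unobserved phases will be generated, and a fuller document may prevent it. But the article does more than leave detail out. It states a method for missing data without condition, and followed literally that method gives a misleading result in a foreseeable case.

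The article also has safeguards: a visit on the second baseline day and a further one if needed, contact after missed entries, review of the diary in sessions, and questionnaires at post-treatment and follow-up. These reduce missingness or give a cross-check. They do not change how the remaining days are filled.

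A reader might infer three stronger claims that the article does not support.

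- *A participant who relapses and leaves would count as a lasting responder.* There is no responder definition and no endpoint for maintained effect. The distortion falls on that person's series and its effect estimate.
- *Stopping treatment triggers the problem.* Only stopping the diary does. Nothing says that prompts end when sessions end.
- *The bias always favours the treatment.* The article does not show that people who stop reporting have relapsed. The size and sign depend on use after the stop, on relapse days already recorded, and on a state-space model that is not named.

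**Conclusion.** The point holds as a conditional one. As written, the rule extends to a permanently stopped diary, where it can only extrapolate. It could present up to a full intervention tail and the whole post-treatment month as data: 65 of 107 days for a stop on treatment day 42. How far the reduction is then overstated rests on assumed figures. With 70%, 40% and 70% of days, a flat projection reports -30 points in both phases against -16 and 0. If use after the stop stays at the treated level, there is no error in the mean. The number of participants who would be affected is unknown, because the article gives no drop-out rate. With ten series, one or two would matter to the conclusion. The change is worth making before the data are analysed; confidence is medium, because a fuller plan may already limit the rule.

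**What to change.** Amend the missing-data provision as follows.

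1. Impute only gaps with answered diary days on both sides.
2. Leave days after the last answered diary unimputed, and report a post-treatment phase without diaries as not observed.
3. Add a sensitivity analysis that sets days after a permanent stop to the participant's own baseline level. It must accompany item 2, because truncation alone leaves the intervention-phase estimate uncorrected.
4. For these participants, report the post-treatment SumID-Q, AUDIT and DUDIT, where collected, beside the diary result.

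The cost is analysis-plan wording and use of data already scheduled. Series become shorter, and the result may be less favourable for participants who stop the diary. The baseline level in item 3 rests on only 7 to 11 diary days, so it is imprecise and belongs in a sensitivity analysis, not in the main estimate.

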## Discussion

3

Take it Personal!+ has the potential to fill the gap in the SUD treatment for individuals with MID-BIF and SUD. Take it Personal!+ is a personalized treatment that differentiates between SUD-related personality profiles of clients. In the multiple baseline across individuals design we aim to test the effectiveness of Take it Personal!+ in decreasing SU.

### Strengths and limitations

3.1

The study contains several innovative elements and strengths. First, Take it Personal!+ is the first personalized SUD treatment supported by mHealth application for individuals with MID-BIF. Second, Take it Personal!+ is based on theoretical frameworks (i.e., MI, CBT, and the four personality profiles) that have shown positive results in a range of studies on SUD [9,[17], [18], [19], [20],^22^]. Third, Take it Personal!+ is responsive to the learning style and needs of individuals with MID-BIF. The CBT is adjusted to the needs of individuals with MID-BIF (e.g., simplified communication), and the design of two sessions a week ensures repetition. Moreover, individuals with MID-BIF experience difficulties in the generalization of treatment to everyday life. In Take it Personal!+, both the confidant from the participant's social or professional network and the mHealth application play essential roles in the treatment and increase the transfer-of-treatment to everyday life.

A common criticism of Single-Case Experimental Designs is the lack of generalizability of the results. In the current study the generalizability of the results is increased in different ways. First, we use direct replications (e.g., same therapist) and systematic replications (e.g., different participants’ characteristics, different therapists, and different settings) [38,41]. The extent to which the intervention effect is comparable across different replications will provide information about the generalizability of the results [27,41]. Second, the characteristics of the participants will be described precisely, which will increase the generalizability by the possibility to apply the intervention to clients with similar characteristics. Lastly, social validity will be assessed and reported [41]. Another strength of the study is that the daily diary method will generate many data points. According to the standards of single-case designs, each phase should have at least 3 data points to allow for time series analyses, but ideally, 5 or more data points should be included [42]. In this study, each phase has more than 5 data points. Another strength is the overlap between the treatment and the data collection, which minimizes the burden of the research for participants. The treatment also requires individuals to register SU in a daily diary. The answers to the daily diary questions for the research will be shared with the therapist, who will discuss them in the treatment sessions.

The study also has some limitations. First, most of the outcome data will be based on self-reports (i.e., questionnaires and daily diary measures), which could lead to a measurement error due to response bias. However, most studies on SU use self-reports, and an earlier study showed that the results of the SumID-Q did not differ from biomarker analysis [43]. Another limitation is that as far as we know, this is the first study to apply daily diary measures in people with MID-BIF for a longer period of time. However, the feasibility, validity, and reliability of this method has been tested in adults with intellectual disabilities [44]. In this study participants filled out more questionnaires in one day for a shorter period of time. Based on this study, and the fact that more questionnaires in one day is more burdensome to complete as compared to one measure a day, the expectation is that the daily diary method for a longer period of time is applicable in people with MID-BIF.

## Ethics approval and consent to participate

The study was approved by the Faculty Ethics Committee of the Radboud University (ECSW-2019-033). All participants sign the informed consent form and if necessary parents or legal representatives also sign the informed consent form.

